To date, we have not identified longitudinal studies that delve into the analysis of all these personal aptitudes and their impact on health in our population. And yet, consideration of the interrelation of personal aptitudes and determinants of health is essential. Even more, there is solid evidence to support the association of socioeconomic, cultural, and environmental determinants with lifestyles, certain risk factors, and diseases (51). In the framework of the WHO 25 × 25 strategy, a recent meta-analysis of 48 cohorts that included 1.7 million people compared persons with low versus high socioeconomic status. Overall mortality rates were higher in the first group (hazard ratio, 95% confidence interval of 1.42, 1.38–1.45 in men, and 1.34, 1.28–1.39 in women), who also had those lifestyles that caused higher premature mortality (52). Other recent findings have shown that social and emotional support can protect health and well-being. However, further research should explain the reasons for this association, and understand its context and mechanisms (53). One of the most highlighted social determinants is the social capital, which refers to the resources available to individuals and groups through social networks (54, 55). Greater social capital has been associated with a better subjective perception of health and well-being (56, 57). Several observational studies indicated that higher social capital is a protective factor against mental and physical health, and mortality (58–60). Another conditioning factor is the working environment (13). Work stress has been associated with worse health status (61), increased risk of depressive disorders (62, 63), sleep disturbances (64), coronary heart disease (65), musculoskeletal pathology (66), alterations of lipid metabolism, and increased metabolic syndrome markers (67).

We believe that the analysis of the causal relationship between personal aptitudes and the adoption of healthy lifestyles, improvements in self-management of chronic conditions, quality of life, incidence and control of risk factors, incidence of chronic diseases and mortality is of special interest, and the creation of a cohort from Primary Health Care (PHC) is a most appropriate framework.

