**Figure 1 fig1:**
[figure not shown]
Diagram showing the causal relationship proposed in the study between the independent variables (personal aptitudes), the dependent variables (morbidity, lifestyles, quality of life, use of services and mortality) and the modulating effect of the covariates.

This is a multicenter study for the creation of a prospective cohort of persons assigned to Primary Healthcare (PHC) centers within nine autonomous communities (AACC; Catalonia, the Basque Country, Castilla y León, Aragón, Galicia, the Balearic Islands, Castilla La Mancha, Andalusia and Madrid). Follow-up examinations and evaluations will be at 5 and 10 years from the entry date.

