### Participants

2.2.

We will include persons aged 35–74 years assigned to the above-mentioned PHC centers, selected by random sampling. Exclusion criteria will apply to persons with a terminal condition or institutionalized at the time of recruitment; persons with intellectual disabilities, dementia, or language difficulties; and persons who plan to move out of Spain within 5 years from study initiation.

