### Variables

2.4.

All the questionnaires used in the study are validated in Spanish except for the LOC, which will be assessed by a single question not yet validated. Table 1 shows the name of the questionnaire, the number of items, and the citation.

**Table 1 tab1:** Validated questionnaires used in the study.

Optional self-administration in our study	Questionnaires	Number of items	Reference of validated version in Spanish
	*Independent variables* *(Personal aptitudes)*		
Yes	Sherer’s general self-efficacy scale (GSES-12)	12	(74)
No	Patient Activation Measure (PAM)	13	(46)
Yes	10-item Connor-Davidson Scale	10	(75)
No	Health Literacy (HLS-EU-Q16)	16	(76)
No	10-Item Big Five Inventory (BFI-10)	10	(77)
	*Covariables*		
Yes	Functional social support (Duke-UNC-11)	11	(78)
Yes	WHO Disability Assessment Schedule (WHODAS 2.0)	12	(79)
Yes	List of Threatening Events (LTE)	12	(80)
Yes	Effort-Reward Imbalance questionnaire (DER/ERI)	16	(81)
	*Dependent variables*		
No	Adherence to the Mediterranean diet (Predimed and Predimed Plus)	23	(82, 83)
Yes	International Physical Activity Questionnaire (IPAQ)	4	(84)
Yes	Pittsburgh Sleep Quality Index (PSQI)	11	(85)
Yes	Quality of Life (EuroQol 5D–5 L)	5	(86)
No	Generalized anxiety disorder (GAD-7)	7	(87)
No	Depression Test Questionnaire (PHQ-9)	9	(88)
No	Depression Risk Calculator (PredictD)	2 + 12	(89)

The independent variables in this study refer to personal aptitudes, will be measured at baseline, and are listed as follows with the corresponding measurement tools: self-efficacy, which will be measured with the Sherer’s general self-efficacy scale (74); activation, measured with the Patient Activation Questionnaire (PAM) (46); resilience, measured with the abbreviated version of the 10-item Connor-Davidson scale (75); health literacy, evaluated with the HLS-EU-Q16 literacy questionnaire (76); LOC, assessed with the statement “I feel that events in my life are often determined by factors that are beyond my control” which has 6 response options in a Likert-type scale; personality characteristics will be examined using the 10-Item Big Five Inventory (BFI-10) for determination of personality traits (77).

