The evaluation of the participants’ mental health will also include the following: a questionnaire on the generalized anxiety disorder (GAD-7) (87), which evaluates the presence of symptoms; examination of the diagnostic criteria for major depression, using the PHQ-9 (88); and estimation of the risk of depression (89), in participants with no diagnosis of a major depressive episode.

We will evaluate the several lifestyles: adherence to the Mediterranean diet, assessed with the PREDIMED (82) and PREDIMED plus (83) questionnaires; type of diet, determined by asking the participants if they follow any specific diet (e.g., vegetarian, vegan); level of physical activity, assessed with the International Physical Activity Questionnaire (84); smoking habit, measured with the 4-question scale adapted from the WHO MONICA study (90); alcohol consumption, considering the total units during the past week and a question on the monthly frequency of excessive consumption (binge drinking) over the past year; and sleep, evaluated using the Pittsburgh Sleep Quality Index (85), the overall number of sleeping hours, usual bedtime, and waking-up time.

The quality of life will be determined using the EUROQol 5D-5L health questionnaire (86), and a question on self-perceived well-being. Finally, the utilization of health services for the last 12 months previous to inclusion into the study will be extracted from electronic health records. Where the research team may have no access to electronic health records, the utilization of health services will be assessed with a survey answered by the participants. The items will enquire on the number of visits (to the emergency department, primary care, and other specialties), hospital admissions, diagnostic tests, and pharmacological treatment (medication, dose, total daily dose, and duration).

Additionally, we will consider the following groups of covariates: sociodemographic, social, functional capacity, and stress level.

We will register the following sociodemographic variables: date of birth, sex, sex orientation, and gender identity (SOGI questions), marital status, nationality, and employment status. We will also consider occupational social class, defined with the educational level and occupation. Participants will answer questions on employment conditions (six items), domestic and care work (six items), income level and economic situation (four items), and housing and material situation.

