### Statistical analysis

2.6.

The statistical analysis will include a descriptive analysis. Percentages of the categorical variables will be calculated for each AACC. Continuous variables with a normal distribution will be described with the mean (standard deviation, SD); otherwise, the median (first and third quartile) will be used. The analyses will be stratified by sex. Bivariate analyses will be performed using the *t*-test for independent samples, or the Mann–Whitney test when required, to analyze continuous variables; and the Chi-squared test for proportions.

Objective one will analyze the incidence of morbidity, defined as the onset of any new condition out of the 17 considered. To this end, a Cox model will be built for each independent variable, and adjusted for the above-mentioned covariates. Potential heterogeneity between AACC will be estimated by introducing random effects in the model. Sensitivity analyses will examine loss to follow-up rates. Objective two will analyze the incidence of the rest of the dependent variables (except incidence of morbidity) using also Cox models, one for each of the six independent variables, adjusted for the covariates. We will calculate the incidence of all-cause mortality and its Kaplan–Meier, stratified by the categorical variables and AACC. Potential heterogeneity will be estimated, and sensitivity analyses performed as in objective one.

Before obtaining the follow-up information at 5 and 10 years, we will describe and analyze the gathered data at baseline. To this end, general linear multilevel models will be used to examine the association of the dependent variables (lifestyles, quality of life, and use of services), with the six independent variables, adjusted for the registered covariates (age, sex, occupational social class, social capital, functional capacity, and stress level). Potential disparities between AACC will be captured by including random effects in the models.

Statistical significance will be considered at *p*-values < 0.05. The analyses will be carried out using the Statistical Package for the Social Sciences (SPSS) version 26.0, and the R-software.

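### The mortality models have no named check on existing illness that could both lower aptitude scores and cause early deaths; two cheap sensitivity analyses would supply one

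*Protocol article*

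**What the plan says.** - **Exposure.** Section 2.4: "The independent variables in this study refer to personal aptitudes, will be measured at baseline". Self-efficacy, activation, resilience and locus of control are self-reports.
- **Clock.** Section 2.1: "Follow-up examinations and evaluations will be at 5 and 10 years from the entry date". No lag or landmark is stated.
- **Mortality analysis.** Section 2.6: "We will calculate the incidence of all-cause mortality and its Kaplan–Meier, stratified by the categorical variables and AACC", plus one Cox model per aptitude.
- **Covariates.** Section 2.4: "we will consider the following groups of covariates: sociodemographic, social, functional capacity, and stress level". Section 2.6 lists age, sex, occupational social class, social capital, functional capacity and stress level for the baseline models. Baseline morbidity is recorded, but its only stated use is to decide which later conditions count as incident.
- **Sensitivity analyses.** Objective one: "Sensitivity analyses will examine loss to follow-up rates". Objective two, which contains mortality: "Potential heterogeneity will be estimated, and sensitivity analyses performed as in objective one".
- **Who is kept out.** Section 2.2: "Exclusion criteria will apply to persons with a terminal condition or institutionalized at the time of recruitment". Persons with dementia, intellectual disability or language difficulties are also excluded.
- **Intended reading.** The Introduction speaks of "the analysis of the causal relationship between personal aptitudes and the adoption of healthy lifestyles" and carries the list on to chronic disease and mortality. The Figure 1 legend also presents the proposed relationship as causal.

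**The concern.** A person with serious but non-terminal disease, or disease not yet recognised, may rate their self-efficacy, activation, resilience or control over events lower because of it, and is also more likely to die in the first years. The Cox model then credits low aptitude with deaths that the illness caused. The distortion runs in the hypothesised direction (better aptitudes, lower mortality), so the result itself would not reveal it. An analysis of loss to follow-up cannot detect it either, because these people are fully followed until death. The same can happen for incident conditions with a long hidden phase, such as dementia, Parkinson's disease and cancer. What is at stake is how far an aptitude-mortality association can carry the causal reading that the article gives it.

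**Working it through.** **The plan's own figure.** The stated sample size is 3,083. With 60% incidence in the non-exposed, RR 1.1 (66%), two-sided 0.05, power 0.80, the stated group ratio and division by (1 - 0.30), a binomial log-RR variance gives 3,060 to 3,064. That is within 3%. It is sized on morbidity; here it serves only as the cohort size.

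**Assumed inputs.** The article gives no mortality rate, so all of these are assumptions:
- true HR of 1 for the aptitude;
- base death hazard 0.0055 per year;
- a share f = 5% or 10% with illness under way, whose hazard is multiplied by 8 in years 0-2 and by 1.5 afterwards;
- illness lowers the score by d = 0.3 or 0.5 SD;
- no adjustment for WHODAS and no losses.

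**Formula.** With q the share of deaths that come from the ill, log HR per SD lower aptitude ≈ d(q - f) / [1 + f(1 - f)d²].

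**Worked case, f = 10%, d = 0.5.**
1. Ten-year risk, not ill: 1 - exp(-0.055) = 0.0535.
2. Ill: cumulative hazard 0.0055 × (8×2 + 1.5×8) = 0.154, so risk 0.1427.
3. Overall: 0.9×0.0535 + 0.1×0.1427 = 0.0624, or about 192 deaths in 3,083.
4. q = 0.01427/0.0624 = 0.229.
5. log HR = 0.5 × (0.229 - 0.10)/1.0225 = 0.063, so HR ≈ 1.07.
6. z = 0.063 × √(192 × 1.0225) = 0.88. Rejection = Φ(0.88 - 1.96) + Φ(-0.88 - 1.96) ≈ 14%.

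**Same case without the first 2 years.**
1. Two-year risks are 0.0109 (not ill) and 0.0842 (ill), overall 0.0183. So 0.0183/0.0624 = 29% of deaths are dropped.
2. The ill supply (0.01427 - 0.00842)/(0.0624 - 0.0183) = 0.132 of later deaths and are 0.1×0.9158/0.9817 = 0.093 of those still at risk.
3. log HR = 0.5 × (0.132 - 0.093)/1.02 = 0.019, so HR ≈ 1.02 and rejection about 6%.

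**All four cases, by the same formula, with repeated simulation of the Cox model:**

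| Ill | Shift | HR per SD | Rejection, formula | Rejection, simulation |
|---|---|---|---|---|
| 10% | 0.5 SD | 1.07 | 14% | 14-17% |
| 10% | 0.3 SD | 1.04 | 8% | 6-9% |
| 5% | 0.5 SD | 1.04 | 8% | 7-9% |
| 5% | 0.3 SD | 1.02 | 6% | 6-9% |

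In the simulations the 0.3 SD range covers both prevalences. After the lag, the HR is at most about 1.03 and rejection is about 5-6%.

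**Why a lag alone is not enough.** Treat the aptitude as low/high with 58.3% low (the article's health-literacy figure), base hazard 0.5% per year, 10% ill at 8 times the hazard for all ten years, and 80% of the ill scoring low.
- The ill are 0.1×0.8/0.583 = 13.7% of the low group and 0.1×0.2/0.417 = 4.8% of the high group.
- Ten-year survival, low: 0.863×exp(-0.05) + 0.137×exp(-0.4) = 0.913.
- Ten-year survival, high: 0.952×exp(-0.05) + 0.048×exp(-0.4) = 0.938.
- Ratio of -log survival = 0.0914/0.0643 = 1.42. Dropping 2 years leaves 1.41.
- If the excess lasts only 3 years, the ten-year ratio is 1.16, and 1.00 once those 3 years are dropped.

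A lag deals with short-lived excess. Lasting illness needs adjustment for baseline morbidity.

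**What the lagged comparison can resolve.** At an assumed 6% mortality, 3,083 × 0.06 = 185 deaths, or about 130 after the lag. The SE of log HR per SD is 1/√185 = 0.074 and 1/√130 = 0.088. A move from 1.07 to 1.02 is 0.068 - 0.020 = 0.048, less than either SE. Power for a true HR of 1.2 falls from Φ(0.182/0.074 - 1.96) ≈ 70% to Φ(0.182/0.088 - 1.96) ≈ 55%.

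**The case against.** **It is an omission from a condensed article.** Extra sensitivity analyses are commonly left to a full protocol or SAP, and the article does not say that loss to follow-up is the only one. That carries weight: the accurate statement is that it is the only one named. But section 2.6 does settle what mortality receives, by pointing back to objective one, so the text is not merely silent.

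**The time origin is not stated in the Cox paragraph.** Correct. It is inferred from baseline measurement and follow-up dated from entry.

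**There are safeguards.** The exclusions remove the most ill. WHODAS 2.0 tracks current illness burden, and stress and life events are adjusted for. Baseline examination, blood tests, anxiety and depression scales and cognitive evaluation make undetected disease less likely. All of this stands and shrinks the bias. It does not close the gap, because functional capacity is not diagnosis and recorded morbidity is not among the covariates.

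**The causal reading is overstated.** The objectives ask about independent association, the Discussion speaks of prognostic factors, and mortality is a secondary objective. This limits the weight of the point. The causal wording in the Introduction and the Figure 1 legend remains.

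**A stronger reading is tempting:** that reverse causation would make the mortality result an artefact, or that an association which vanishes after a lag should be disowned. The article does not support the first, since nothing in it fixes the size of the bias. The second would discard real effects, given the loss of power shown above.

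**Conclusion.** The point holds as a cheap improvement of modest size. Nothing stated in the article separates an effect of low aptitude on mortality from illness that lowers the score and causes early death, and the bias would favour the hypothesis. Its size is unknown. The illustration gives HR 1.02 to 1.07 per SD and rejection of 6% to 17% with no true effect. It rests wholly on assumed mortality, illness prevalence, hazard multipliers and score shift, and it ignores the WHODAS adjustment, so it leans to the high side. A reader might take the 1.42 as the likely bias; it needs 10% of the cohort at eight times the hazard for ten years, and no figure in the article points there. Nor does the article justify saying that the study cannot inform a causal question at all. It shows only that the named analyses do not address this particular route.

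**What to change.** In section 2.6, pre-specify for the mortality models:
1. a repeat that excludes the first 2 years of follow-up;
2. a repeat that adds baseline morbidity as a covariate.

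Repeat (1) for incident morbidity where dated record diagnoses are available. Section 2.4 describes conditions active at the visit and does not say that onset dates are collected, so this should be confirmed first.

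Report lagged and unlagged hazard ratios side by side with confidence intervals. Set no rule based on the association disappearing or losing significance. If the estimate clearly attenuates, limit the causal wording of the Introduction and the Figure 1 legend accordingly.

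**Cost.** For mortality, the planned models are re-run on data that the study already means to hold. The lagged analysis loses about 25-30% of deaths in the illustration and has a wider interval, and the assumed 30% loss to follow-up would widen it further. Adding baseline morbidity may over-adjust if low aptitude contributed to that morbidity. Both should therefore remain sensitivity analyses, with the main model unchanged. Choosing the 2-year lag now, before follow-up data exist, avoids a post hoc choice.

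### The baseline analysis assigns general linear multilevel models to every outcome, including 12-month counts and a nominal diet variable; it should name generalized linear models with a family per outcome

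*Protocol article*

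**What the plan says.** Section 2.6 of the protocol article plans an analysis of the baseline data before any 5- or 10-year follow-up is available. One model family is named for three outcome domains: "general linear multilevel models will be used to examine the association of the dependent variables (lifestyles, quality of life, and use of services". The models are to be "adjusted for the registered covariates (age, sex, occupational social class, social capital, functional capacity, and stress level", and regional differences are handled in the same way for all outcomes: "Potential disparities between AACC will be captured by including random effects in the models". No link function, distribution, transformation or recoding is given.

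Section 2.4 defines the outcomes in those domains. For service use in the previous 12 months, "The items will enquire on the number of visits (to the emergency department, primary care, and other specialties), hospital admissions, diagnostic tests, and pharmacological treatment". The lifestyles include "type of diet, determined by asking the participants if they follow any specific diet (e.g., vegetarian, vegan" and "smoking habit, measured with the 4-question scale adapted from the WHO MONICA study", and also a question on how often in a month the participant drinks to excess. Other lifestyle measures are scores or quantities: Mediterranean diet adherence, physical activity, sleep quality, hours slept and alcohol units. Quality of life is measured with EQ-5D-5L and a well-being question.

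**The concern.** General linear model is the standard name for a model with an additive mean and normal errors of constant variance. Several listed outcomes do not have that form. An unordered category has no mean to model. A count has a variance that grows with its mean, is bounded at zero, and often responds to covariates multiplicatively.

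This is a method the article states, not detail it leaves out. The descriptive and bivariate steps of the same section do separate outcome types (medians or the Mann–Whitney test where needed, chi-squared for proportions), but the adjusted model does not. At stake are the cohort's adjusted baseline associations with service use and lifestyles: whether diet type can be modelled at all, whether the intervals for visits and admissions are accurate, and how much power those comparisons have.

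**Working it through.** **1. Outcomes against the stated model**

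| Outcome (section 2.4) | Type | Normal-error linear model |
|---|---|---|
| Visits, admissions, tests over 12 months | counts | poor fit |
| Type of diet | unordered categories | not without recoding |
| Smoking | coding not stated | workable if yes/no; not if unordered with several categories |
| Binge frequency | coding not stated | depends on coding |
| Diet, activity and sleep scores, hours, alcohol units, EQ-5D | scores or quantities | broadly reasonable, with attention to skew |

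**2. The variance problem in numbers.** For an over-dispersed count, Var(Y) = m + αm². Assume an average of 6 visits, α = 1, and a standardised covariate z acting as m = 6·exp(0.5z − 0.125).
- At z = +1: m = 6 × 1.455 = 8.73; variance 8.73 + 76.21 = 84.9.
- At z = −1: m = 6 × 0.535 = 3.21; variance 3.21 + 10.31 = 13.5.

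The ratio is 84.9/13.5 = 6.3. The linear model assumes it is 1.

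**3. The plan's own figure.** The article gives no power calculation for the baseline models. Its only calculation, 3,083 participants, is for 10-year incident morbidity. With risks 0.60 and 0.66 (RR 1.1), k = 1,793/1,290 = 1.390, two-sided 5%, 80% power and 30% loss:

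n₀ = [1.96·√((1 + 1/k)·p̄q̄) + 0.842·√(p₀q₀ + p₁q₁/k)]² / (0.06)² = 871

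Then 871/0.7 gives 1,245, and 1,245 × 2.390 = 2,975 in total. A continuity correction gives 3,073 and a log-RR formula 3,060, both within 1% of 3,083. The figure is sound for its purpose and serves below only as n.

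**4. Simulated power for counts.** Taken from the article: n = 3,083, 58.3% exposed (inadequate or problematic health literacy), 5% significance. Assumed, because the article gives none: mean μ, dispersion α, rate ratio (RR), and the log-scale SD s of one covariate independent of exposure. The generating model is m = μ·exp(x·ln RR + s·z − s²/2), with counts Poisson given m times a gamma variable of mean 1 and variance α. The linear model with model-based errors is compared with a negative binomial model with log link.

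| μ | α | RR | s | Replicates | Linear % | Neg. binomial % | Loss, points |
|---|---|---|---|---|---|---|---|
| 6 | 1.0 | 1.1 | 0 | 1,000 | 66.5 | 67.0 | 0.5 |
| 6 | 0.8 | 1.1 | 0.5 | 300 | 70.0 | 78.0 | 8.0 |
| 6 | 1.0 | 1.1 | 0.5 | 1,000 | 58.0 | 65.7 | 7.7 |
| 6 | 1.5 | 1.1 | 0.5 | 300 | 40.0 | 51.7 | 11.7 |
| 6 | 0.8 | 1.1 | 0.8 | 300 | 48.3 | 74.0 | 25.7 |
| 6 | 1.0 | 1.1 | 0.8 | 1,000 | 41.9 | 64.0 | 22.1 |
| 6 | 1.5 | 1.1 | 0.8 | 300 | 33.0 | 49.7 | 16.7 |
| 0.5 | 2 | 1.2 | 0.5 | 300 | 65.7 | 70.3 | 4.6 |
| 0.5 | 2 | 1.2 | 0.8 | 300 | 56.3 | 67.3 | 11.0 |
| 0.1 | 3 | 1.4 | 0.5 | 1,000 | 74.1 | 75.9 | 1.8 |
| 0.1 | 3 | 1.4 | 0.8 | 300 | 65.7 | 72.3 | 6.6 |

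With robust (HC1) errors the μ = 6, α = 1.5, s = 0.8 row becomes 35.7 against 49.7, a loss of 14.0. That is the lower end of the range for a strong covariate effect on visits.

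A second set-up used nine region indicators, a skewed disability covariate, and exposure depending on age, class and disability (300 replicates each). It gave 66 against 81 (mean 0.5, RR 1.25), 67 against 87 (mean 7, RR 1.12) and 43 against 54 (mean 0.12, RR 1.3, with 3–4% of fitted values negative). In the first of these the average linear standard error was 0.0434 against an empirical SD of 0.0370, a ratio of 1.17.

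**5. Type I error of the linear model.** The 1,000-replicate runs gave 5.7%, 4.4% and 2.6%. The last had a strong covariate correlated with exposure, and HC1 errors brought it to 4.3%. The sixteen 300-replicate null runs lay between 3.3% and 7.7%, with a Monte Carlo standard error of √(0.05 × 0.95/300) = 1.3 points. In the 7.7% run the negative binomial model gave 7.0%. The second set-up stayed at or below 5%.

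**6. Yes/no smoking.** With logit(p) = −1.3 + 0.22x + 0.3z, power was 70.8% for the linear model and 71.0% for logistic regression (1,000 replicates).

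**The case against.** The wording may be loose for generalized linear models. The article names no normal distribution, it separates data types in its bivariate tests, and a condensed article may leave families and codings to a fuller plan. That is fair as a guess at intent. It does not remove the point, because the sentence names a family that does not fit several listed outcomes, and if generalized was meant the same correction is needed.

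A reader might go further and infer that smoking cannot be analysed. The documents do not support this: the coding is not stated, and a yes/no coding works almost as well in a linear model. Nor can it be stated as fact that service-use comparisons lose much power. The article gives no means, dispersion, rate ratios or covariate strengths, and the loss is close to nil in some plausible settings.

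It is also true that a difference in mean visits is a legitimate quantity to estimate, and that robust errors repair much of the variance problem. They recovered little of the lost power here (43.2% against 41.9% in the μ = 6, α = 1, s = 0.8 row). The simulations themselves favour the negative binomial model somewhat: they generate data from it, the main set treats dispersion as known, and neither set uses the planned regional random effects.

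**Conclusion.** The point holds as a mismatch between a stated model and the outcomes assigned to it. Without recoding, an unordered multi-category outcome such as type of diet cannot be fitted. For counts, the linear model misstates the variance, can give standard errors that are too large and negative fitted use, and can lose power.

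In the main simulations the loss is about 0 to 2 points with no covariate effect or for rare admissions with a moderate one, about 8 to 12 for visits with a moderate covariate effect, and about 14 to 26 with a strong one. Rarer events with a strong covariate, and the second set-up, fall within that overall span. All these figures rest on assumed distributions. The top value is the least certain: it comes from 300 replicates in a setting where the negative binomial null rejection rate was 8.7%. The 1,000-replicate run at α = 1 gave 22.1.

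The evidence does not show inflated false-positive rates, so the tests should not be called invalid. The Cox analyses of objectives one and two and the sample size do not depend on these models.

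**What to change.** In section 2.6, replace the general linear wording with generalized linear multilevel models, keep the same covariates and regional random effects, and name the family by outcome:

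- negative binomial with log link for counts of visits, admissions and tests;
- logistic, ordinal or multinomial for smoking, type of diet and binge frequency, with the coding of each stated;
- linear for approximately continuous scores, with robust standard errors where the distribution is skewed, such as EQ-5D.

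The cost is a few lines of text and slightly more analysis; R, already named in the article, fits these models. Results will be rate ratios and odds ratios in place of mean differences. If absolute differences are wanted, marginal mean differences can be reported from the same models.
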